Verbal consent will be confirmed at the start of the telephone interview, including consent for audio-recordings. The consent form will be read and audio recorded along with patient replies which will also be ticked on paper. Participants can still take part in the telephone interview, even if they do not wish to be recorded, in which case responses would be recorded on paper. A study ID will be assigned prior to transcription to ensure the interview is anonymised. The consent form will be stored separately to the anonymised study data.

A designated contact person who is external to the study team has also been nominated if prospective participants wish to discuss any concerns that invitees may have regarding the study before giving consent. The Patient Information Sheet will make clear that participants may withdraw from the study at any time without giving a reason and their data will be removed from the study.

Based on previous research [8], it is expected that 25% will respond and be randomised, we expect a further 20% attrition between consent and questionnaire return.

The risk information materials will initially be pilot tested in around 30 participants from the screening database. Therefore, 144 will be invited, with 36 expected to respond and 30 completing the questionnaire.

Following the pilot testing in sample participants, a further 1440 will be invited to receive the finalised personalised risk information about their risk of having colorectal cancer and provide responses. As above, it is expected that 360 will respond and be randomised, with 300 then completing the study questionnaire. Figure 1 shows a flow diagram of the study design with expected numbers of participants. A small number of participants would be purposively sampled, from those consenting to be telephoned, from each treatment arm, estimated at 10 per arm, total = 30, to provide representation with regard to age, gender, socioeconomic status and responses to the scenarios.

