An *n* = 300 (100 in each group) will have 83.7% power of detecting a 1 point increase in knowledge (intervention versus control), and a 2 point difference in attitudes (based on existing study means/SDs [9, 15]), using a one-way ANOVA. A pilot sample of 60–100 per group is recommended to provide an estimate of an event rate [22] (e.g. screening uptake); so a sample of 300 would provide an indicative effect size of colonoscopy uptake for a future full-scale study. We would send out 1440 invitations, from whom we conservatively expect to get around 360 replies (25%) (based on previous research [8]); we expect a further 20% attrition between consent and questionnaire return, giving a final *n* = 300. In the event that we do not hit our target of 360 replies to the first letter, a second wave of invitation letters would be sent out (the number of these would be based on actual response to and the deficit from the first invitation). We accept that the sample size may not be sufficient to assess all interactions between covariates. However this is a pilot study and a major aim is to assess effect sizes to determine accurate sample sizes for a larger study; we believe we have sufficient power to achieve this aim.

There is a risk of causing upset to patients with cancer or patients who may be disturbed by thinking about their cancer risk. It is not possible to exclude such patients from the initial contact. We have worded the Participant Information Sheet to express our apologies for contacting anyone in inappropriate circumstances. The patient invitation letter provides contact details of an individual who is completely independent of the research who can help in this case and advise to whom a complaint can be made to if required. It will also be stressed that risk scenarios are purely hypothetical. It should be noted that all individuals who will be contacted are enrolled in screening and the invite would not be dissimilar to the Scottish Bowel Screening invite.

If there is a problem with any participant it will be recorded in an Adverse Event log in compliance with TASC SOP11v9.

The PI will seek approval for any amendments to the Protocol or other study documents from the Sponsor, Research Ethics Committee (REC) and NHS R&D Office(s). Amendments to the protocol or other study docs will not be implemented without these approvals.

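### With 20% attrition, 360 replies yield 288 completed questionnaires (96 per arm), not the stated 300, and the second-wave trigger of 360 replies does not guard against the gap

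*Protocol article*

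**What the plan says.** The recruitment text in the Methods of the protocol article gives the rates: "it is expected that 25% will respond and be randomised, we expect a further 20% attrition between consent and questionnaire return". It then applies them to the main study, with 1440 invited: "it is expected that 360 will respond and be randomised, with 300 then completing the study questionnaire". The pilot of the materials uses the same ratios: "144 will be invited, with 36 expected to respond and 30 completing the questionnaire".

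The sample-size paragraph, later in Methods, repeats the chain. It expects about 360 replies (25%) from 1440 invitations, and then "we expect a further 20% attrition between consent and questionnaire return, giving a final" n of 300. The power statement rests on that 300: "100 in each group) will have 83.7% power of detecting a 1 point increase in knowledge", by one-way ANOVA, together with a 2-point difference in attitudes. The same paragraph cites 60–100 per group as the recommended size for a pilot sample.

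The top-up rule follows: "In the event that we do not hit our target of 360 replies to the first letter", a second wave of letters goes out, sized on the response to the first wave and the deficit from it. No top-up in the article is tied to the number of questionnaires returned.

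**The concern.** The attrition is described as loss between consent and questionnaire return, so it is a share of those who consented and were randomised. On that reading, 20% off 360 cannot leave 300. The same step appears in two places in Methods, and 360 is then used as a firm recruitment target, so this is neither a typing slip nor loose rounding.

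Two things are at stake. First, the final n that carries the 83.7% power claim is not what the plan's own rates deliver. Second, the top-up rule is keyed to 360 replies, the number that results from the faulty step. A trial that performs exactly as planned would fall short of its stated n, and the rule would call for no more letters. The study also aims to supply sample sizes for a larger trial, and the same inflation step should not be carried into that planning.

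**Working it through.** **Inputs, all from Methods of the protocol article:** 1440 invitations; 25% reply and are randomised; 20% attrition between consent and questionnaire return; final n = 300 (100 per arm, three arms); power 83.7% by one-way ANOVA. The article gives neither alpha nor standard deviations.

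**1. Replies.** 1440 × 0.25 = 360. This reproduces the stated figure.

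**2. Completed questionnaires.** Completed = randomised × (1 − attrition) = 360 × 0.80 = 288, and 288 / 3 = 96 per arm. The stated 300 is not reproduced. The gap is 300 − 288 = 12, and 12 / 300 = 4%.

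**3. Where 360 comes from.** 300 × (1 + 0.20) = 360 matches exactly. The step that fits 20% attrition is 300 / (1 − 0.20) = 375. Read the other way, the attrition implied by 360 and 300 is 1 − 300/360 = 16.7%.

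**4. What 300 would need at the stated rates.** 375 replies, and 375 / 0.25 = 1500 invitations, which is 1500 − 1440 = 60 more letters.

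**5. Pilot.** 36 × 0.80 = 28.8 against the stated 30. The pattern is the same, but the gap is about one participant.

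**6. Power at 288.** For a one-way ANOVA with three groups, power = P(F′ > critical F), where F′ is noncentral F with 2 and n − 3 degrees of freedom and noncentrality n·f². Because alpha and the SDs are not given, I assume alpha = 0.05 and solve for the f that gives 83.7% at n = 300.

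| n | f | n·f² | Power |
|---|---|---|---|
| 300 | 0.1885 | 10.66 | 83.7% (by construction) |
| 288 | 0.1885 | 10.24 | 82.1% |

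The loss is 83.7 − 82.1 = 1.6 percentage points. Repeating this with alpha = 0.01, again solving f from 83.7%, gives 81.7% at n = 288, so the result hardly depends on the assumed alpha.

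**7. Chance of reaching 300.** If each randomised person returns the questionnaire independently with probability 0.80, the number returned is binomial.

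- From 360: P(at least 300) = 6.2%; the central 95% range is 273 to 303.
- From 375: P(at least 300) = 53.1%.

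The second figure is close to one half because 375 × 0.80 = 300. The comparison shows only that 375 centres the plan on 300 and 360 does not.

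**The case against.** The strongest reply is that very little follows from the error. Twelve questionnaires are 4% of the target, power stays above 80%, and 96 per arm lies inside the cited 60–100 per group. The study calls itself a pilot whose major aim is to assess effect sizes. All of this stands, and it limits the weight of the point. It does not make 360 × 0.80 equal to 300.

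A second reply is that the 360 is described as approximate and conservative. That helps only in part, because the next sentence uses 360 as the target that decides whether more letters are sent.

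Three stronger readings are tempting and are not supported:

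- **That the trigger locks in the shortfall.** It does not. Replies are not capped at 360, and anyone who returns the response form is to be randomised. A response above 25%, or attrition of 16.7% or less, could still reach 300. The trigger fails to guard against the expected shortfall; it does not guarantee one.
- **That the study is underpowered.** The 82.1% rests on an assumed alpha and a back-solved effect size, and even so it does not fall below 80%. The 6% chance of reaching 300 should not be read as a chance of failure either, since it treats 300 as a hard threshold and 20% as a known rate. The expected result is a near miss.
- **That the pilot numbers are a second error to correct.** The article describes the pilot as about 30 people and attaches no power claim to it, so 28.8 is immaterial.

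**Conclusion.** The point holds as an arithmetic inconsistency with a small effect. At the plan's own rates, the expected number of completed questionnaires is 288 (96 per arm), 12 fewer than stated, and the second-wave trigger of 360 replies leaves that gap open when recruitment goes exactly to plan. The headcount result depends only on reading attrition as a share of those randomised, which is how the article words it. The power result, about 82.1% instead of 83.7%, depends on the assumed alpha of 0.05 and on the effect size (f about 0.189) implied by the article's own power figure. No analysis or conclusion of the study is threatened. The numbers should still be corrected, because a stated sample size and a recruitment rule both rest on them.

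**What to change.** Choose one of these and apply it to the recruitment text and the sample-size paragraph together:

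1. Restate the expected final n as 288 (96 per arm), with power of about 82%, recalculated from the alpha and SDs actually used.
2. If attrition of about 16.7% was meant, state that in place of 20%; 360 and 300 then agree.
3. Keep 300 and 20%, and either set the reply target and second-wave trigger at 375 (about 1500 invitations) or tie the trigger to returned questionnaires.

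Check that the flow diagram, which is not visible in the text reviewed, carries the same numbers. The pilot figures need no separate correction.

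Options 1 and 2 cost only an edit. Setting the target at 375 under option 3 costs about 60 more letters, and about 15 more participants to randomise (375 − 360).

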## Discussion

This early phase study will examine patient responses to personalised risk information about their risk of having CRC. The best methods to present personalised risk information based on age, gender and faecal haemoglobin concentration will be determined and compared to current practice i.e. a positive/negative test result. We will test whether this can lead to truly informed choice, the effect on intention to have a colonoscopy and thus potential impact on colonoscopy services, and whether informed choice can improve patient outcomes/satisfaction and potentially save lives.

Our study will be based on hypothetical scenarios and intention, rather than actual uptake of colonoscopy. Thus, we expect to use the results to inform a full-scale RCT which will evaluate actual uptake of colonoscopy for Scottish Bowel Screening programme participants. If successful, the intervention could be low-cost to deliver at scale, and thus prove cost-effective for introduction within the national screening programme.

## Abbreviations

ANOVA: Analysis Of Variance
CRC: Colorectal cancer
FIT: Faecal Immunochemical Test
GCP: Good Clinical Practice
gFOBT: Guaiac Faecal Occult Blood Test
PI: Principal Investigator
PPI: Public and Patient Involvement
RCT: Randomised Controlled Trial
REC: Research Ethics Committee
SIMD: Scottish index of multiple deprivation
SOP: Standard operating procedures
TASC: Tayside Medical Science Centre
